## *IV.B. Intervention and routine activities*

To prepare the implementation of interventions, a workshop with the health area responsables for vector control and a workshop with formal and informal community leaders will be held to discuss the detailed implementation planning, as also a meeting with the population of every health area involved to inform them about the trial and answer questions concerning tools and its implementation.

Insecticide treated Curtains (ITC):

The insecticide-treated curtains (ITC) to be used are made from long-lasting, insecticide treated (pyrethroid deltamethrin is applied during manufacture) polyester netting that requires no re-impregnation (PermaNet®; Vestergaard-Frandsen company). PermaNet materials are special UV protected and retain their insecticidal properties and efficacy for about 2 years (information from producer). The material has been approved by WHOPES for use as bednets. ITC will be distributed in each house to be placed in door-openings inside the house or on the closet or on the wall where no or minimal sunshine will touch the material - if a curtain is already hanging, the project-curtain can be attached to it. Per house a maximum of 3 curtains will be distributed, except for schools, working areas and public spaces where more curtains can be distributed.

All curtains will be white patterned netting and have a 1.1m width*2.9m height size (people can adapt them according their needs).

Before distribution the consent of the users will be procured in a community meeting and a written informed consent-form will be obtained (annex 1).

The curtains will be distributed with an accompanying promotion campaign: a Frequently Asked Questions document (FAQ) is already elaborated (annex 2). It will be given to all included households in the ITC arm and will be discussed during distribution on individual basis.

The curtains will be distributed to the houses, but also public places, as working areas, schools, cultural centra will be included as far as possible.

A replacement of curtains will be foreseen for the curtains becoming damaged during use. If new persons are coming to live in the house-blocks during the study, they will be approached to be included in the study.

The procedure of distribution is detailed in annex 3.

Peri-focal insecticide spraying (PFS)

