In all arms, the routine control activities will be continued. In the control-arm, this will be the only strategy. The standard control activities are carried out by the programme’s vector control workers: entomological surveillance and source reduction through periodic inspection of houses, larviciding (with temephos) of water-holding containers, selective adulticiding (cipermethrine and clorpiriphus-fogging) when *Aedes aegypti* foci are detected, providing health education, promotion of community based environmental management and enforcing mosquito control legislation through the use of fines.

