## *IV. C. Data collection and analysis*

Effect measures:

Primary outcomes:

Effectiveness: Breteau Index, House index, Pupae per person index, (adult mosquito infestation)

confirmed Dengue cases (if any). Comparison of infestation at each time point between the intervention arms, taking into account the pre-intervention infestation levels and the cluster design. Generalized linear random effect regression models with a negative binomial link function will be used.

Secondary output:

Uptake and use of ITC

Acceptance of PFS and ITC (and identification of underlying lay dimensions of acceptability)

Change in intra-and extradomiciliary risks for Aedes infestation

Cost- effectiveness of ITC and of PFS

Residual insecticidal activity of deltamethrin applied in ITC and in PFS

Data collection:

1. Baseline study (in both intervention and control arms) :
   1. Entomological survey:

Existing of larval and pupal surveys; the larval surveys will be conducted as in the routine system (exhaustive inspection of all houses and potential water holding containers on the presence of immature stages of Aedes). The traditional Stegomyia indices will be calculated: the House Index (HI) and Breteau index (BI). Collection of adult mosquitoes: during routine surveys, the vector control teams are also inspecting houses in the search of adult mosquitoes.

The pupal surveys will consist of direct inspection of potential water-holding containers inside and around the houses following the recommendations of Focks (Focks 2004). This will be done by a special team in 20% of the house-blocks (randomly chosen: 23 houseblocks/arm). All containers where immature stages of Aedes are detected will be emptied and the absolute number of pupae will be counted. For elevated water tanks a sweeping method will be used to collect the majority of the pupae. The total number of positive containers for Ae. aegypti pupae and their relative contribution to total pupal production will be recorded and computed. The number of persons per house will be also enquired (during the distribution of tools) for the construction of Pupal Index per inhabitant (PPI) at the cluster level.

- 1. Evaluation of main intra and extra domiciliary risks at household and environmental risks at community level in each houseblock included in the study: data collected by the routine vector control programme teams through observation, guided by an observation guide (Annex 5).

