  2. Evaluation of resistance of the local Aedes strains to the four groups of adulticides commonly used for mosquito control (report, including methodology, in annex 6).

1. Follow-up surveys:
   1. Entomology (in both intervention and control areas):

The same measurements as in the baseline entomological study will be done once intervention started (House Index (HI), Breteau index (BI), Pupal Index per inhabitant (PPI)). The frequency of the larval surveys (including the collection of adult mosquitoes) will be according the cycles taking place by the routine control programme, with at least one survey per month. The pupal surveys will take place twice a year during the peak periods of infestation (end of April and end of September).

- 1. Surveillance of Dengue cases (confirmed) and epidemiology of clinical Dengue cases if an epidemic occurs in the period of study (in both intervention and control areas)
  2. Observation of main intra and extra domiciliary risks at household and environmental risks at community level (data collection as explained above; frequency once/year) – (Annex 5) (in both intervention and control areas)
  3. Uptake and use of curtain (in ITC intervention area)

Uptake and continued use will be evaluated every 4 months over a period of 2 years. The teams will use an observation guide during the household visits (Observation guide: annex 7).

- 1. Registration of executed vector control activities: besides information available in reports of the *Aedes* control programme, information will be obtained from community perspective (Questionnaire: annex 8) (in both intervention and control areas)

Every 4 months, one in 30 households will be questioned concerning the vector control activities (by community or by routine vector control programme) that were realized in the previous period.

- 1. Evaluation of acceptance, use and satisfaction of specific control measure (in intervention areas):
     1. ITC: through household surveys, 4 , 12, 24 months after distribution (in a sample of 400 houses, systematic random sampling – able to detect a 50% acceptance with 5% precision) (data collection form: annex 9)
     2. PFS: through household surveys, 4 , 12, 24 months after distribution (in a sample of 400 houses, systematic random sampling – able to detect a 50% acceptance with 5% precision) (data collection form: annex 10)
  2. Residual activity/bio-availability testing (in intervention areas):

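### The person count for the pupae-per-person index, a listed primary outcome, is tied to tool distribution, so the protocol names no occasion for collecting it in the control arm

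*Protocol*

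**What the plan says.** Protocol IV.C lists as primary outcomes "Effectiveness: Breteau Index, House index, Pupae per person index, (adult mosquito infestation"), and then confirmed dengue cases. The numerator of the PPI comes from pupal surveys: "This will be done by a special team in 20% of the house-blocks (randomly chosen: 23 houseblocks/arm"). The denominator is given in the same paragraph: "The number of persons per house will be also enquired (during the distribution of tools) for the construction of Pupal Index per inhabitant (PPI"), with the index to be formed for each cluster.

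That paragraph belongs to the part introduced as "Baseline study (in both intervention and control arms"). The follow-up part, introduced as "Entomology (in both intervention and control areas"), repeats the baseline measurements and names them: "House Index (HI), Breteau index (BI), Pupal Index per inhabitant (PPI"). The PPI is therefore wanted in all three arms, before and after the interventions start.

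Protocol IV.B says that routine control continues everywhere and adds for the controls: "In the control-arm, this will be the only strategy". In the curtain (ITC) arm, "ITC will be distributed in each house". In the spraying (PFS) arm, houses are treated every 4 months. Both tools need written household consent. The qualitative study in IV.C expects to interview some household heads who declined the tool at the start.

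**The concern.** The PPI is a ratio, so both of its parts must be collected in the same way in every arm. Pupae are counted by one special team in all arms. Residents are to be asked about at an event that belongs to two arms only. A field team following the text literally would have no instruction to count residents in control houses. A team that filled the gap from another source would give the comparator arm a denominator of a different kind.

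At stake are the PPI contrast of each tool with control, and the cost-effectiveness ratio if the PPI is the index used there. A statistical analysis plan cannot repair this. Who is asked, when and in which arm is a matter of fieldwork, and a resident count not taken at the visit cannot later be restored for the same house and round.

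**Working it through.** **1. Every stated contact that might yield a count of residents (Protocol IV.B and IV.C).**

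- Tool distribution: ITC and PFS arms only. It is the only contact at which persons per house are said to be asked.
- Pupal survey: all arms, 23 house-blocks per arm. It is described as inspecting containers and counting pupae; no count of residents is mentioned.
- Routine larval survey: all arms, at least monthly. It covers containers and adult mosquitoes; no count of residents is mentioned.
- Observation of domiciliary and environmental risks (annex 5): all arms, yearly. Annex not shown.
- Questionnaire on vector control activities (annex 8): all arms, one household in 30 every 4 months. Annex not shown. A 1-in-30 sample would not by itself give a count for each inspected house.
- Acceptance surveys: 400 houses for each tool, intervention areas only.

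The main text thus names no source for control houses.

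**2. Timing (Timeline).** Pupal surveys fall in five months: year 1 months 4 and 9, year 2 months 4 and 9, year 3 month 4. Curtains are distributed in year 1 month 4 only. Spraying falls in year 1 months 4 and 9, year 2 months 1, 5 and 9, and year 3 month 1. A count tied to distribution would coincide with one of five pupal rounds in the ITC arm, three of five in the PFS arm, and none in the control arm. The opportunity to count differs between all three arms.

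**3. What unequal counting would do.** Let q be residents recorded divided by residents actually living in the houses whose pupae are counted. Then

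observed PPI ratio (tool/control) = true ratio × q(control) / q(tool).

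The protocol gives no q and no PPI target. For illustration, assume a true ratio of 0.50, borrowed from the 50% reduction aimed at for the Breteau Index:

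- q(control) = 1 and q(tool) = 0.95, 0.90, 0.80: 0.50/0.95 = 0.53, 0.50/0.90 = 0.56, 0.50/0.80 = 0.63.
- q(tool) = 1 and q(control) = 0.95, 0.90, 0.80: 0.50 × 0.95 = 0.48, 0.50 × 0.90 = 0.45, 0.50 × 0.80 = 0.40.
- Equal q in both arms: 0.50.

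The error can run either way or vanish.

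**4. Sample size.** Protocol IV.A uses the Hayes-Bennett method with 0.02 and 0.01 positive containers per house, 250 houses per cluster and k = 0.5. Two-sided 5% and 80% power are assumed here, as neither is stated:

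c = 1 + (1.96 + 0.84)² × [(0.02 + 0.01)/250 + 0.5² × (0.02² + 0.01²)] / (0.02 − 0.01)²
= 1 + 7.85 × (0.000120 + 0.000125)/0.0001 = 1 + 19.23 = 20.23.

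This agrees with the stated 20; 20 × 1.05 = 21 and 3 × 21 = 63 follow. No person count enters the formula.

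**The case against.** The strongest reply is that the plan plainly intends the PPI in control clusters: the sentence stands in a part covering all arms, and follow-up names the index again. The parenthesis might mark a period rather than a visit, since the first pupal survey, the curtain distribution and the first spraying share year 1 month 4. Annexes 3, 4, 5 and 8 are not shown, and one of them may record residents. This stands to the extent that a reader may not conclude that the PPI cannot be computed in the control arm, or that 21 of 63 clusters lack a denominator. What can be said is that no source is stated.

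A reader might also infer that the tool-arm denominators are selective. The text does not say so. Curtains are meant for every house, a refusing household can still be asked how many people live there, and a house closed to both teams drops out of numerator and denominator together. Nor does the text say that the count is taken once: follow-up repeats the baseline measurements, spraying visits recur, and newcomers are to be approached.

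Finally, the PPI is only one of several primary outcomes, and the Breteau Index, which drives the sample size, is counted per house. That is correct and limits the reach of the point. It does not reconcile a primary outcome required in all arms with a counting occasion that two arms have and one lacks.

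**Conclusion.** The point holds as a gap in how a primary outcome is to be collected. The protocol requires the PPI in all three arms but states an occasion for counting residents in only two. For the tool arms it leaves open whether houses that refuse or are missed are counted, and whether counts are renewed at later pupal rounds.

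No size or direction of bias can be assigned. It is tempting to say that the PPI is inflated in the tool arms by 1/(1 − r) when a share r of residents is missed, which gives 5%, 11% or 25% for r of 5%, 10% or 20%, and that this works against the tools. That reading needs an assumed r, full pupal inspection of the missed houses and a complete control denominator. The documents give none of these.

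The conclusion rests on the main text alone; an annex that records residents in all arms would reduce it to a correction of wording. The pupal counts, the Breteau and House indices and the planned 63 clusters are not touched. The cost-effectiveness ratio is exposed only if the PPI is the index chosen for it.

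**What to change.** In Protocol IV.C, delete the parenthesis that ties the person count to the distribution of tools. State instead that the pupal survey team records the number of residents in every house it inspects, with the same question in all three arms and at each pupal round, and that this same-house, same-round count is the PPI denominator. A house that is not inspected then contributes neither pupae nor persons, whether or not it accepted a tool.

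The change should be in place before the first pupal round. The cost is one extra question per inspected house on an existing visit. At 250/5 = 50 houses per block, 23 blocks are about 1,150 houses per arm, or 3 × 1,150 = 3,450 short answers per round. No other figure in the protocol changes.

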K-Othrine 25 WG, supplied by Bayer Environmental Sciences co. (25% deltamethrin formulation) will be sprayed every 4 months (3 times/year). It is a granular formulation that need to be solved into water (20 gram in 8 Liter of water, sufficient to treat 200 m² and attaining 25 mg a.i./m²). It has a long lasting residual activity. Where deposits remain undisturbed, residual activity depends upon the nature of the surface (Rojas de Arias et al. 2004;Rozilawati et al. 2005). Sustained residual activity beyond 12 weeks post-application is observed on non-porous surfaces. Deltamethrin is photostable and the particulate suspension enhances availability to insects.

The insecticide will be sprayed on the outside of the ground-level water tanks and the walls behind them; and on the adult *Aedes* resting sites (for example under beds, in and under closets) in the intradomestic area.

Teams of health workers of the routine *Aedes* control programme will be trained to realize this activity and standard operating procedures are designed. A short movie has been made to show the correct application of insecticide to all implementers. Control visits by supervisors will be done on a regular basis during application to assure quality of action.

The PFS will be done in the houses, but also public places, as working areas, schools, cultural centra will be included as far as possible.

Before distribution the consent of the users will be procured in a community meeting and a written informed consent will be obtained on the moment of spraying. Information on the product and its possible side effects will be provided to the communities in the preparative community meetings and to each household before spraying starts.

The procedure of implementation is detailed in annex 4.

The set-up of the ITC and PFS interventions will be done by a local research group and by the routine vector control programme. The former will be responsible for its implementation, coordination with the local health authorities, documentation of process and organization of training sessions according to the needs of the actors involved.

Routine *Aedes* Control activities

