We will collect during the assay the financial cost of the routine vertical programme and will calculate the average cost per house inspected and treated.

For each arm, we will multiply the number of houses inspected and treated annually during the study by the corresponding average cost described above, to calculate the total annual cost of the routine programme per arm.

We will calculate the total economic cost of the new control tools (ITC and PFS): The economic cost of the community participating in the set up, the financial and economic cost of the routine programme during set up, distribution, installation and maintenance of the tools; and the economic cost of the community participating in collective vector control activities.

The total annual cost of the different arms can be obtained adding the cost of the routine programme and the economic cost of the implemented strategy.

We also will calculate the average and marginal cost per house within arms and incremental cost per house between arms.

The activities of vertical programme will be costed prospectively every month during two years of the study, as well as the cost regarding the distribution of the tools itself, every time it happens (see annex 11-12-13-14-15-16). The cost information about participation in individual and collective activities related to vector control of the community will be followed by questions included in the acceptability survey 3 times during follow up period, in 400 houses per arm for the two intervention arms and with quarterly surveys on the routine activities done (annex 8 ).

We will obtain the effectiveness measure from the entomological and epidemiological study and use the difference of differences between the baseline data and the data for the subsequent periods as effectiveness measure.

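### Routine control is costed with one undefined average per house, which can misprice differences between arms in fogging triggered by foci

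*Protocol*

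**What the plan says.** Protocol section III.B, objective 3, compares the cost-effectiveness of both tools with the routine strategy. The costing rule is in section IV.C, under cost-effectiveness evaluation:

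- From the financial cost of the routine programme, the investigators "will calculate the average cost per house inspected and treated".
- The rule for turning this into an annual routine cost, arm by arm, then reads: "we will multiply the number of houses inspected and treated annually during the study by the corresponding average cost described above".
- The arm total is obtained by "adding the cost of the routine programme and the economic cost of the implemented strategy".

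No unit cost is named for inspection, larviciding or fogging. The section does not say whether the average is trial-wide or per arm, or whether a house that is inspected but not fogged counts as treated.

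Three other places bear on the rule:

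- Section IV.C describes the routine larval survey as "exhaustive inspection of all houses and potential water holding containers", with follow-up surveys at least monthly in intervention and control areas.
- Section IV.B lists, among routine activities, "selective adulticiding (cipermethrine and clorpiriphus-fogging) when" foci of the vector are found. Larviciding is listed for water-holding containers, without such a trigger.
- The sensitivity analysis in section IV.C varies the tool price and uses the variation in the relation between coverage and entomological outcome. Routine cost is not among the inputs varied.

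**The concern.** An incremental analysis needs the routine cost of each arm to move with the work actually done there. The number of houses inspected is set by arm size and survey cycles, so it should be nearly the same in every arm (21 × 250 = 5250 houses). The one routine activity that the protocol ties to infestation is focal adulticiding. If its cost is spread over all inspected houses through a single average, a tool that reduces foci shows no saving on routine work, and the incremental cost shrinks to the cost of the tool.

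At stake is the numerator of the incremental cost-effectiveness ratio (ICER) for objective 3. The planned sensitivity analysis would not expose the problem, because it leaves routine cost fixed. The entomological outcomes are not affected.

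**Working it through.** The protocol states no routine cost, so there is no figure to reproduce. The check applies the stated rule under its possible readings to a simple cost model.

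**Inputs from the protocol (sections IV.A and IV.C).** Breteau index 2 per 100 houses at baseline and 1 per 100 as the target; equal arms of 5250 houses; surveys at least monthly, taken here as 12 a year.

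**Assumptions, not in the protocol.**
- The Breteau index serves as foci per house-visit: p₀ = 0.02 in control and p₁ = 0.01 in each tool arm.
- Houses fogged per focus, m: 1 to 20.
- Cost of fogging a house relative to inspecting it, r: 0.5 to 3.
- The cost of one inspection visit is set to 1.

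**Formulas.** Houses fogged per house-visit: f = p × m. Routine cost per house-year: 12 × (1 + f × r). True saving per house-year: 12 × (p₀ − p₁) × m × r = 0.12 × m × r.

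**Credited saving by reading.**
- A. One pooled average × houses inspected: 0, since the counts are equal.
- B. Arm-specific average × houses inspected: the full saving.
- C. Separate averages for inspected and treated houses, each × its own count: the full saving.
- D. One pooled average u × (inspections + treatments): 12 × u × (f₀ − f₁) = 0.12 × m × u, with u = [(1 + f₀r) + 2(1 + f₁r)] / [(1 + f₀) + 2(1 + f₁)] over one control and two tool arms.

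**Worked case, m = 10 and r = 3.** f₀ = 0.2 and f₁ = 0.1. Control: 12 × 1.6 = 19.2. Tool arm: 12 × 1.3 = 15.6. True saving: 3.6, or 3.6/19.2 = 18.8% of control-arm routine cost. Under D, u = (1.6 + 2.6)/(1.2 + 2.2) = 4.2/3.4 = 1.235, and the credited saving is 12 × 1.235 × 0.1 = 1.482.

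Savings per house-year, in inspection-visit costs:

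| m | r | True saving (also B, C) | % of control routine cost | A | D |
|---|---|---|---|---|---|
| 1 | 0.5 | 0.06 | 0.5 | 0 | 0.119 |
| 10 | 0.5 | 0.6 | 4.5 | 0 | 1.129 |
| 10 | 1 | 1.2 | 8.3 | 0 | 1.2 |
| 10 | 3 | 3.6 | 18.8 | 0 | 1.482 |
| 20 | 3 | 7.2 | 27.3 | 0 | 3.411 |

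The pattern under D is general in this model. Because u is a weighted mean of 1 and r, the saving is over-credited when fogging a house costs less than inspecting it (r < 1), exact when r = 1, and under-credited when r > 1.

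The error in incremental cost is the true minus the credited saving. Under A it is the whole saving. Under D with m = 10 it is 0.6 − 1.129 = −0.529 at r = 0.5 (tools favoured) and 3.6 − 1.482 = 2.118 at r = 3 (tools penalised).

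**The case against.** The strongest reply is that the sentence need not mean a single pooled average. The count is taken for each arm and includes houses treated, and *corresponding* may point to an arm-specific average or to one average for inspected and another for treated houses. Under either (B or C above), averted fogging is credited in full. The costing forms (annexes 11 to 16) are not shown and may already separate the activities. This reply stands against any claim of built-in bias. It does not remove the ambiguity: the text describes one average, in the singular, and its possible readings run from no credit to full credit.

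A reader might infer three stronger points, none of which the protocol supports:

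- *That the ICER is biased against both tools on every reading.* Only reading A has that direction throughout, and only if the tools reduce foci. Reading D can favour them; B and C carry no such bias.
- *That averted larviciding is also lost.* Section IV.B attaches no infestation trigger to larviciding, so it should not be listed as an averted cost.
- *That an arm-specific average would count staff time twice.* Section IV.B does say that "Teams of health workers of the routine" programme are trained to spray, and section IV.C places the programme's cost of delivering the tools under tool cost. But tool distribution is costed as an item of its own, and nothing says the same hours also stay in routine cost. Double counting is possible and worth excluding in words; it is not shown.

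It can also be said that a unit-cost breakdown belongs in an analysis plan. That would answer a silent protocol. Here a formula is stated, and it is the formula that needs repair.

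**Conclusion.** The point holds as a defect in a stated costing rule. On the pooled reading, the rule misprices differences between arms in foci-triggered fogging. With a count of inspected houses, the error goes against the tools and equals the whole saving; with treatments added to the count, it can go either way.

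All of this is conditional on the tools reducing foci. If they do not, there is no saving to misprice. The halving used above is the design target, not a known effect.

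The size cannot be derived from the protocol. The 0.5% to 27.3% range rests on the assumed m and r and on treating the Breteau index as foci per house-visit. Nor can it be turned into money: the only price given is USD 1.9 per curtain distributed (section II), and no routine cost per house stands beside it. A percentage error in the ICER should therefore not be quoted.

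The correction is worth making because objective 3 depends on the rule and the change is cheap.

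**What to change.** In section IV.C, under cost-effectiveness evaluation:

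1. Replace the single average by separate unit costs for house inspection, larviciding and focal adulticiding. Multiply each by that activity's recorded count in each arm.
2. State that programme hours spent delivering curtains or perifocal spraying are counted only under tool cost, and are removed before routine unit costs are formed.
3. Add the routine unit costs to the inputs varied in the sensitivity analysis.

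The cost is small. Section IV.C already has programme activities costed every month and executed activities registered in intervention and control areas. The downside is that activity counts must be tallied by arm. If the costing annexes already make this split, the change is one of wording.

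### The arm-cost rule charges community participation in vector control only to the ITC and PFS arms, so each tool's incremental cost against routine control is overstated by whatever community cost the control arm incurs.

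*Protocol*

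**What the plan says.** All of the costing text is in Protocol section IV.C, under cost-effectiveness evaluation.

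- **Routine programme:** "We will collect during the assay the financial cost of the routine vertical programme". It is assigned to arms by volume: "For each arm, we will multiply the number of houses inspected and treated annually during the study by the corresponding average cost described above".
- **New tools:** an economic cost is defined for ITC and PFS only. It has three parts. The first is the community's cost in setting the tools up. The second is what the programme itself spends and uses to introduce the tools and keep them working. The third is not tied to the tools by its wording: "and the economic cost of the community participating in collective vector control activities".
- **Arm total:** it "can be obtained adding the cost of the routine programme and the economic cost of the implemented strategy".
- **Source of community cost data:** questions in the acceptability survey, three times, "in 400 houses per arm for the two intervention arms and with quarterly surveys on the routine activities done" (annex 8).

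Three other places bear on this. Section IV.B (routine *Aedes* control) says that routine work is the control arm's sole strategy, and that this work includes encouraging community environmental management. Section IV.C (registration of executed vector control activities) runs annex 8 in control as well as intervention areas and asks about activities by the community as well as by the programme: "Every 4 months, one in 30 households will be questioned concerning the vector control activities". Specific objective 3 (section III.B) is the cost-effectiveness of both tools against routine control.

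**The concern.** Community time spent on collective vector control is background activity that can occur in any arm. If it is counted in the tool arms and left out of control, it does not cancel in the arm difference and is charged to the tools. That difference is the numerator of the ICER, so the error goes straight into the answer to specific objective 3.

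Nothing else in the plan would expose it. The bootstrap interval reflects sampling variation, not an omitted cost item. The planned sensitivity analyses vary the tool price and the relation between coverage and entomological outcome, and neither touches the control arm's cost.

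**Working it through.** The protocol gives no arm cost, unit cost or ICER, so there is no figure to reproduce. The check is an algebraic reading of the cost rule.

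**Notation, per house.** R = routine programme cost at financial value; S = tool cost, including set-up time of programme and community; Ct and Cc = community cost of collective vector control in a tool arm and in control.

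**Step 1: increment against control, with equal routine volume.**

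- As planned: (R + S + Ct) − R = S + Ct
- With community cost in both arms: (R + S + Ct) − (R + Cc) = S + Ct − Cc
- Difference: Cc

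S is a true increment and causes no bias. Only the collective-activity term does. The ICER denominator is unchanged, so the percentage error in the increment is also the percentage error in the ICER.

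**Step 2: illustrative size.** Cc is not in the documents. Assume S = R = 1 (arbitrary units) and vary Ct and Cc. The overstatement is Cc / (S + Ct − Cc).

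| Ct | Cc | Planned | Corrected | Overstatement |
|---|---|---|---|---|
| 0.1 | 0 | 1.1 | 1.10 | 0% |
| 0.1 | 0.05 | 1.1 | 1.05 | 4.8% |
| 0.1 | 0.10 | 1.1 | 1.00 | 10% |
| 0.1 | 0.15 | 1.1 | 0.95 | 15.8% |
| 0.3 | 0 | 1.3 | 1.30 | 0% |
| 0.3 | 0.15 | 1.3 | 1.15 | 13.0% |
| 0.3 | 0.30 | 1.3 | 1.00 | 30% |
| 0.3 | 0.45 | 1.3 | 0.85 | 52.9% |

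**Step 3: ITC against PFS.** Both arms follow the same rule, so R + S + Ct is compared with its counterpart and no community term is missing on either side.

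**Step 4: financial-only valuation of routine work.** Let the full economic value be R(1 + u), and let routine volume in the tool arm be v times that in control. Planned minus full difference: (v − 1)R − (v − 1)R(1 + u) = (1 − v)uR. At v = 1 this is 0 for any u. With assumed u = 0.2 it is +0.02R at v = 0.9 and −0.02R at v = 1.1; with u = 0.5 it is +0.05R and −0.05R.

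**Step 5: data available for control.** Houses per arm: 21 × 250 = 5250. Annex 8 at one in 30: 5250 / 30 = 175 per arm per round. The timeline shows six rounds (months 6, 10, 14, 18, 22 and 26), so 6 × 175 = 1050 interviews per arm. The tool arms also have 3 × 400 = 1200 acceptability interviews each, which control does not have.

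**Step 6: frequency.** The timeline rounds are 4 months apart, in line with the 4-monthly wording and not with the quarterly one. Six rounds with 4-month recall cover 6 × 4 = 24 months; with 3-month recall they would cover 6 × 3 = 18.

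**The case against.** The strongest reply is that the collective-activity item stands in a list headed by the cost of the new tools. It may therefore mean only community time that the tools cause, in which case no background cost is charged. This reading is possible but not stated. It also fits poorly with the same section's plan to follow participation in individual and collective vector control generally, partly through annex 8.

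It can also be said that annex 8 already covers control areas, so the data are planned. That stands, and it narrows the gap: what is missing is a control-arm term in the arm total, not a data source. Encouragement by programme staff does not by itself show that control residents give much time, so Cc could be small. Cost-effectiveness is a secondary output, and costing detail may sit in an analysis plan that is not shown. But the protocol itself fixes the arm-total rule, and fixes it asymmetrically.

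Three stronger readings are tempting and are not supported:

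- **That the tools' incremental cost is certainly and materially inflated.** The error equals Cc, which no document reports.
- **That mixing financial and economic valuation biases the comparison as a whole.** Step 4 shows that it cancels at equal routine volume and otherwise goes either way; tool set-up time is properly incremental.
- **That the error can be sized in money or annualisation factors.** The 1.9 USD per curtain in the introduction comes from a cited cost study, three curtains is a maximum per house, and no community cost is given to set against it. Nor does the protocol say that survey rounds will be multiplied by four.

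**Conclusion.** The concern holds in conditional form. Under the rule as written, the incremental cost of ITC and of PFS against routine control is overstated by Cc, the control arm's community cost of collective vector control. The direction is fixed wherever Cc is above zero; the size is unknown. The 0% to 53% range in the working rests on assumed relative costs and is not an estimate for this trial. The conclusion assumes that the collective-activity item is not confined to tool-caused time, which the protocol does not say.

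ITC versus PFS is untouched by this asymmetry. Financial-only valuation of routine work is a lesser matter that arises only if routine volume differs between arms. The conflict over annex 8 frequency is a separate inconsistency in the text and stands whatever the view on the arm totals.

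**What to change.** 1. State one costing perspective and apply it to all three arms.
2. Add community participation cost, taken from annex 8, to every arm total including control. Alternatively, count only tool-attributable community time in the tool arms and say so. The first option is preferable: the second gives the same increment only if background community activity is equal across arms.
3. Use the 400-house acceptability surveys for tool-specific time only, so that background participation is measured with the same instrument in every arm.
4. Reconcile the quarterly and 4-monthly descriptions of annex 8 with the timeline, and set the recall period so that the rounds add up to the year.

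Cost: amended wording, a little more analysis and, if annex 8 (not shown) lacks them, a few cost or time items on a questionnaire already planned in all arms. No new survey is needed.
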